**STUDY DESIGN**

This study is a prospective independent cohort, observational study examining the relationship between poor sanitation practices and adverse pregnancy outcomes.

**Objective (s)**

The primary aim of the study is to assess the risk of APO associated with poor sanitation access and practices using a population-based pregnant cohort, with specific aims:

1) To quantify the prevalence of open defecation practices among pregnant women at their first trimester.

2) To investigate the relationship between poor sanitation practices and adverse pregnancy outcomes.

**Study Settings**

Coastal rural (Balianta & Balipatana Blocks of Khurda District) and Mainland tribal (Kuarmunda and Lathikata Blocks of Sundargarh District) in Odisha, India.

**Sample Size and Power of the Study**

Previous research conducted at AIPH suggests that birth of a low birth weight infant occurs in approximately 20% of all pregnant women, of which 12-14% are preterm. We estimate that a sample size of 582 women should give us 80% power to detect a 1.5 fold increase in risk of APO if the mother practices open defecation during her first trimester of pregnancy, at a significance level of 95% (using a two tailed test). Estimating an anticipated 15% dropout, our final sample size is planned to be 670. The sample size was calculated using the following formula (Fleiss, 1981)

INCLUDEPICTURE "http://www.statsdirect.com/help/content/image/stat0072_wmf.gif" \* MERGEFORMATINET
[figure not shown]

Where

INCLUDEPICTURE "http://www.statsdirect.com/help/content/image/stat0073_wmf.gif" \* MERGEFORMATINET
[figure not shown]

Z-alpha= 1.96 at the for alpha of 0.05 i.e. 95% confidence level

Z-beta=0.84 for beta of 0.2 i.e. power of 80%

*P0* is the probability of events in the unexposed (which is approximately 20% APO in our study)

*P1* is the probability of events in exposed (which is estimated to be 30% i.e. 1.5 times in our study)

m= ratio of exposed to unexposed which is approximately 1:1 in our study as the unfavourable sanitation practices (mainly open defecation is believed to be 50%).

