**STATISTICAL ANALYSIS PLAN**

The study will employ an independent prospective cohort, where a random sample (N=670 pregnant women of 10-12 weeks of gestation) will be selected from the population census. Descriptive statistics (frequency, means, and standard deviations) will be calculated for all demographic, anthropometric, clinical outcomes and baseline sanitation behavior variables. The outcome that our analysis will principally work with includes Adverse Pregnancy Outcome (APO) which includes preterm birth (PTB) and low birth weight (LBW), using definitions described previously. The relationship between the main explanatory variable in our study that includes sanitation access and practice, and the principal outcomes (APO, PTB and LBW), all of which are binary will initially be examined using contingency tables and differences in distribution of outcomes across exposure groups tested using Chi-square test. The risk of APOs contingent upon sanitation access and practice will be estimated using appropriate regression analysis. The models will be adjusted for co-variates which are considered *a priori* to be confounders of this relationship, which includes maternal age; BMI, maternal haemoglobin as indicator of maternal nutritional status; and household poverty and educational attainment of the mother as indicators of maternal socio-economic status. Alpha will be set at 0.05 for all tests of hypotheses.

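### At the plan's own 15% dropout, 670 recruits leave about 570 evaluable women, not the 582 behind the 80% power; the effect is about one point of power

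*SAP*

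**What the plan says.** The SAP, under *Sample Size and Power of the Study*, sets the analysable number first: "We estimate that a sample size of 582 women should give us 80% power to detect a 1.5 fold increase in risk of APO", where the raised risk is tied to open defecation in the first trimester. The inputs are listed there. The test is two-sided ("at a significance level of 95% (using a two tailed test"), with "Z-alpha= 1.96 at the for alpha of 0.05 i.e. 95% confidence level" and "Z-beta=0.84 for beta of 0.2 i.e. power of 80" per cent. The 20% risk "is the probability of events in the unexposed (which is approximately 20% APO in our study"; the 30% risk "is the probability of events in exposed (which is estimated to be 30% i.e. 1.5 times in our study". Exposed and unexposed women are taken as roughly equal in number.

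The recruitment figure follows: "Estimating an anticipated 15% dropout, our final sample size is planned to be 670". The step from 582 to 670 is not written out. The section *STATISTICAL ANALYSIS PLAN* carries the figure forward as the number to be selected: "a random sample (N=670 pregnant women of 10-12 weeks of gestation".

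Two rules under *Multiple comparisons and multiplicity* decide what dropout does to the analysis. The item on missing outcome data removes from the final analysis any woman without a baseline or later follow-up measurement. The item on incomplete follow-up keeps whatever was recorded before a woman migrated or withdrew.

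**The concern.** A dropout rate is a share of the women recruited. To end with a given evaluable number, that number is divided by one minus the rate. Multiplying by one plus the rate gives a smaller figure, and 670 is what multiplication gives here. Recruitment would then fall short of the evaluable number that the same section says is needed, at the dropout rate that the same section assumes.

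What is at stake is whether the power statement is true as written. The 582 carries almost no reserve above 80%, so any shortfall takes the design below its stated power. No estimand, test or analysis set is affected.

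**Working it through.** **Inputs** (all from *Sample Size and Power of the Study*): P0 = 0.20, P1 = 0.30, 1:1 allocation, z = 1.96 and 0.84, evaluable total 582, dropout 15%, planned total 670.

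**1. Reproduce 582.** The two-proportion formula with unpooled variance gives, per group:

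n = [P0(1 − P0) + P1(1 − P1)] × (1.96 + 0.84)² / (P1 − P0)²
= (0.16 + 0.21) × 7.84 / 0.01 = 290.08, rounded up to 291.

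Two groups give 2 × 291 = 582, an exact match.

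**2. Reproduce 670.** 582 × 1.15 = 669.3, rounded up to 670. This also matches exactly. Because the SAP does not show the step, the multiplication is an inference from the match.

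**3. Apply the plan's dropout to 670.** 670 × 0.85 = 569.5, about 570 evaluable women. The shortfall is 582 − 570 = 12. This step does not depend on how 670 was reached.

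**4. What loss does 670 cover?** 1 − 582/670 = 88/670 = 13.1%.

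**5. What would 15% require?** 582 / 0.85 = 684.7, so 685. That is 15 more than 670 (15/670 = 2.2%).

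**6. Power, using the formula from step 1.** Power = Φ(0.10 / √(0.37/n) − 1.96), with n per group.

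| Evaluable total | n per group | 0.10 / √(0.37/n) | less 1.96 | Power |
|---|---|---|---|---|
| 582 | 291 | 2.804 | 0.844 | 80.1% |
| 569.5 | 284.75 | 2.774 | 0.814 | 79.2% |

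The cost is 0.9 of a percentage point. The pooled-variance version gives nearly the same loss, from 79.7% at 582 to 78.8% at 569.5, so the size of the effect does not hang on the choice between the two.

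**7. Does dropout reduce the analysed number?** Yes. The rule on missing outcome data excludes women without a follow-up measurement. The rule that keeps earlier data from women who leave cannot supply a birth outcome that nobody observed. The SAP describes no replacement or imputation.

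**The case against.** The best defence is that the discrepancy is trivial beside the looseness of the inputs. The unexposed risk and the exposure split are both given as approximate, and the dropout rate is only anticipated. At 582 women and a risk ratio of 1.5, moving P0 from 20% to 19% lowers power from 79.7% to 77.0% (pooled formula), about three times the effect found here. If loss turns out to be 13% rather than 15%, 670 is enough. All of that stands and it limits the weight of the point. It does not make the three stated figures agree.

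One could also read the 15% as a margin added to 582, in which case 670 follows. But the SAP calls it dropout, and a margin of that size covers a loss of about 13%, not 15%.

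A reader might infer three stronger things that the document does not support:

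- **That 582 is itself wrong, or rests on an unnamed formula.** It reproduces exactly from the stated inputs. The SAP cites its source and prints the formula as images that are not readable in the text at hand, so nothing can be held against it there.
- **That power is really much lower because a continuity correction should apply.** The readable text specifies none. The chi-square test is only the initial look, with adjusted regression to follow. A lower figure obtained that way would come mostly from changing the formula, not from the dropout step.
- **That the study is seriously underpowered or must enrol more women.** A loss of under one point supports neither.

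**Conclusion.** The point holds as a minor arithmetic inconsistency. The figures 582, 15% and 670 cannot all be true together: 15% loss from 670 leaves about 570 women, 12 short, and 670 protects 582 only up to about 13.1% loss. Power at the plan's own dropout rate is about 79%, against the 80% stated.

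This rests on the plan's own event rates, 1:1 split and two-sided 5% level, on the formula that reproduces 582, and on dropout meaning a share of women recruited whose outcomes are then missing from the analysis. That 670 came from multiplying by 1.15 is very likely but inferred, and the conclusion does not need it. The design and the planned analysis are otherwise untouched.

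**What to change.** Amend one sentence in *Sample Size and Power of the Study*, in one of two ways:

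- state that 670 women are recruited, that about 570 are expected to be evaluable after 15% dropout, and that power is then about 79%; or
- keep 582 and 80%, and state that 670 allows for about 13% dropout.

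The first keeps the dropout assumption and gives a slightly less favourable power. The second keeps the power and needs the sponsor to be content with a 13% allowance. Under either, the 670 in *STATISTICAL ANALYSIS PLAN* can stay. The cost is a wording change with no extra enrolment. The figure of 685 matters only if the sponsor chooses to keep both 582 evaluable women and a 15% dropout.

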**Study Outcome Measures**

**A) Primary:** The primary outcome of interest will be the incidence of an adverse pregnancy outcome (APO), defined as an event of either preterm birth (PTB), low birth weight (LBW), or both, spontaneous abortion, and still birth. We will use World Health Organization (WHO) definitions for all primary outcome measures. Preterm birth will be defined as birth of a live baby before 37 completed weeks of gestation or fewer than 259 days since the first day of the woman’s last menstrual period. Neonates weighing < 2500 grams at birth will be considered to be of LBW. Spontaneous abortion will be defined as “fetal loss” before 22 weeks of gestation with gestational age estimated from the participants’ self-reported last menstrual period. Stillbirth will be defined as fetal death after 22 weeks gestation with no sign of life (cord pulsation or muscle movement). Infant demographics such as gestational age, birth weight, and gender of the child should be abstracted from medical charts at delivery by the CHV. The birth data should be recorded into a customized mother-baby tracking cards provided to all pregnant women for future follow-up purposes.

Infant demographics such as gestational age, birth weight, and gender of the child will be abstracted from the birth records by the CHV at the delivery and should be entered individual mother-baby cards. For interpretation purposes we will classify the outcomes into three categories (APO, PTB and LBW). All reported adverse pregnancy outcomes (PTB, LBW, stillbirth and abortions) will be grouped into one category and will be referred as “adverse pregnancy outcomes (APO)”; PTB and LBW may be interpreted separately.

**B) Secondary:** We anticipate studying the following secondary outcomes using the same cohort:

1) Incidence of change of sanitation behaviour

2) Incidence of UTI/BV symptoms

3) Prevalence of anaemia and BMI status among the pregnant cohort

4) Incidence of morbidities such as malaria, gastrointestinal illness etc.

5) Key social, cultural, and economic considerations that serve as motivators and barriers among pregnant cohortto adopt improved sanitation and hygiene practices

**Study Exposure Measures**

**A) Primary exposure assessment:** A household survey with observation (checklist) will be conducted by trained by CHVs addressing specific questions on defecation and hygiene practices and conditions during recruitment and subsequent visits. A similar question will also be asked to record the sanitation practices before pregnancy. To document the number of women using a latrine and variability in their practice, participants will be asked to identify the primary and secondary locations were they had defecated in the last month, and whether there were instances in the past month where they chose not to use the primary defecation site. Visual observations of defecation sites will be performed to confirm the interview response, to inspect for the presence of a functional water source or water storage container at the latrine, and where a latrine was used to document the type of latrine design and inspect for the presence of visible fecal contamination on latrine floors, walls, and stances. Other information such as hand washing practice after defecation, source of bathing water will also be collected.

**B) Collection of Covariates/confounders:** A face to face interview along with personal measurements will be conducted using a structured questionnaire by a CHV to collect maternal age, socio-demographic information, mother's anthropometric characteristics such as height and weight. Ownership of BPL card (a proxy measure for poverty), household characteristics and assets will also be recorded. Maternal hemoglobin at recruitment will be collected from Mother & Child Tracking System card. For women, where this information unavailable, a study supervisor will conduct the haemoglobin estimation from finger prick blood samples using a portable haemoglobin analyzer (HemoCue® Hb 301).

**STATISTICAL ANALYSIS PLAN**

The study will employ an independent prospective cohort, where a random sample (N=670 pregnant women of 10-12 weeks of gestation) will be selected from the population census. Descriptive statistics (frequency, means, and standard deviations) will be calculated for all demographic, anthropometric, clinical outcomes and baseline sanitation behavior variables. The outcome that our analysis will principally work with includes Adverse Pregnancy Outcome (APO) which includes preterm birth (PTB) and low birth weight (LBW), using definitions described previously. The relationship between the main explanatory variable in our study that includes sanitation access and practice, and the principal outcomes (APO, PTB and LBW), all of which are binary will initially be examined using contingency tables and differences in distribution of outcomes across exposure groups tested using Chi-square test. The risk of APOs contingent upon sanitation access and practice will be estimated using appropriate regression analysis. The models will be adjusted for co-variates which are considered *a priori* to be confounders of this relationship, which includes maternal age; BMI, maternal haemoglobin as indicator of maternal nutritional status; and household poverty and educational attainment of the mother as indicators of maternal socio-economic status. Alpha will be set at 0.05 for all tests of hypotheses.

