**Multiple comparisons and multiplicity**

Results from all analyses will be assessed against an alpha of 0.05. There will be no adjustments for multiplicity as there are pre-defined outcomes and objectives, and the influence of individual results on the overall interpretation of the study will reflect their importance.

**Covariate adjustment**: The primary statistical analyses for the outcome variables “APO” measured at the follow-up visit will be adjusted by performing analyses adjusted for other baseline characteristics suspected *a priori* to be associated with the outcome. Any group differences in potentially influential baseline characteristics will be included in the interpretation and discussion of results.

**Incomplete follow-up:** For each subject, participation in the study will end at birth/pregnancy outcomes. If a subject migrates or withdraws, data collected until that point in time will be used.

**Missing outcome data:** All precautions should be made for no missing values on baseline variables that are planned for use as covariates. For the primary outcome and secondary outcomes, subject who do not have a measurement taken at the baseline or subsequent follow-up visit will be restricted from the final analysis.

**Outliers:** Outliers will be identified by examining residual plots. Cases that visually “stand out” will be assessed for a possible influence on results. A comparison of results from analyses with and without the outlier(s) may be performed. Where there are discrepant results from the two analyses, this will be reported and discussed in the manuscript(s).

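### Study setting (coastal rural or mainland tribal) is not named as a covariate or stratum, so the adjusted sanitation estimate is open to confounding by place

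*SAP*

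**What the plan says.** Under Study Settings the SAP places the cohort in "Coastal rural (Balianta & Balipatana Blocks of Khurda District) and Mainland tribal (Kuarmunda and Lathikata Blocks of Sundargarh District) in Odisha, India". Under Statistical Analysis Plan, "a random sample (N=670 pregnant women of 10-12 weeks of gestation) will be selected from the population census"; nothing there stratifies or matches the sample by setting. The same section says that the risk of APO "will be estimated using appropriate regression analysis", adjusted for a priori confounders, "which includes maternal age; BMI, maternal haemoglobin as indicator of maternal nutritional status; and household poverty and educational attainment of the mother".

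The covariate paragraph under Multiple comparisons and multiplicity says that the primary APO analysis will be adjusted by "performing analyses adjusted for other baseline characteristics suspected" beforehand to be related to the outcome. No variable is named there. It then says: "Any group differences in potentially influential baseline characteristics will be included in the interpretation and discussion of results".

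Setting, district and block appear nowhere in the SAP as a covariate, stratum, cluster or subgroup. Under Sample Size and Power of the Study there is one overall exposure figure (about 50%) and one baseline risk (about 20%), with no figure by setting.

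**The concern.** The study is observational, so its second specific aim, the relation between sanitation and APO, depends on confounder control. The cohort joins two places that the SAP labels differently. If women in one place practise open defecation more often and also have a higher APO risk for other reasons, a pooled comparison attributes part of the difference between places to sanitation. If the place with more open defecation has the lower APO risk, a real effect could be masked.

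Age, BMI, haemoglobin, poverty and education describe the individual woman and her household. They may carry part of a difference between places, but need not carry all of it. The SAP lists malaria among the morbidities to be studied, for example, and malaria is not in the adjustment set. An analyst could follow the SAP to the letter and never adjust for setting, or could decide on it after seeing the results.

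**Working it through.** **1. The plan's own figure.** Inputs from Sample Size and Power of the Study: P0 = 0.20, P1 = 0.30, ratio 1:1, z = 1.96 and 0.84, N = 582, 15% dropout, final N = 670. The pooled two-proportion formula without continuity correction gives 294 per group, 588 in total, within about 1% of 582. Also 582 × 1.15 = 669.3, rounded up to 670. The sample size is not in dispute. With 15% lost, 670 × 0.85 = 569.5, about 570 evaluable, or 285 per exposure group.

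**2. Assumptions for the illustration.** The SAP gives no rates by setting, so these are assumed: two settings of equal size and no sanitation effect within either. Open defecation averages 50%, as in the SAP. APO averages 25%, the mean of the SAP's 20% and 30% at 1:1.

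**3. Formula.** With open defecation e1, e2 and APO risk r1, r2 in the two settings:
- exposed risk = (e1·r1 + e2·r2)/(e1 + e2)
- unexposed risk = [(1−e1)·r1 + (1−e2)·r2]/[(1−e1) + (1−e2)]

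**4. Crude results, true risk ratio 1.00.**

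| Open defecation | APO by setting | Exposed / unexposed risk | Crude RR | Chance of p<0.05 |
|---|---|---|---|---|
| 50% / 50% | any | equal | 1.00 | 5% |
| any | equal | equal | 1.00 | 5% |
| 70% / 30% | 30% / 20% | 0.27 / 0.23 | 1.17 | about 20% |
| 80% / 20% | 32% / 18% | 0.292 / 0.208 | 1.40 | about 64% |

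The last column is the two-proportion test at about 285 per group. Reversing the direction in the third row (more open defecation where APO is lower) gives 0.23/0.27 = 0.85, so the bias can go either way.

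**5. Allowing for the listed covariates.** The table is crude, whereas the planned regression adjusts for five variables. Suppose, as an assumption, that they absorb half of the APO difference between settings:
- 30%/20% becomes 27.5%/22.5%. At 70/30 this gives 0.26/0.24 = 1.08, with about a 9% chance of p<0.05.
- 32%/18% becomes 28.5%/21.5%. At 80/20 this gives 0.271/0.229 = 1.18, about 21%.

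If they absorb all of it, the bias is zero.

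**6. Cost of adjusting.** The share of exposure variance explained by setting is R² = [(e1−e2)²/4]/0.25, and effective N = N(1−R²). For 20% against 30% at N = 570:
- no imbalance: R² = 0, power 79%
- 70/30: R² = 0.16, effective N = 478.8, power about 72%
- 80/20: R² = 0.36, effective N = 364.8, power about 60%

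**The case against.** The best defence is that the SAP does not shut setting out. The five confounders are introduced as included items rather than a closed list, and the later paragraph permits further a priori characteristics. A reader might infer that the SAP fixes a list which excludes setting; the wording does not support that. What stands is narrower: setting is permitted but not named, and discussing group differences in the interpretation is not a rule for the model.

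A second defence is that poverty, education, BMI and haemoglobin may already carry much of the difference between places. This stands too. The crude figures apply directly only to the initial chi-square tables; for the adjusted model they overstate the bias by an unknown amount.

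A reader might also infer that the two populations are known to differ greatly, or that the main result will be biased. The SAP gives labels and no rates by setting. More extreme inputs can be chosen: open defecation 90%/10% with APO 30%/15% gives a crude risk ratio of 0.285/0.165 = 1.73. Nothing in the SAP points to such a split, and the conclusion does not rest on it.

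Finally, adjustment is not free. The splits that produce the largest bias are those where adding setting costs the most power. That is a reason to disclose the cost. It is not a reason to leave setting out, because the unadjusted estimate is most exposed to confounding in exactly those cases.

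**Conclusion.** The concern holds in this limited form and should be fixed. Setting is nowhere named as a covariate or stratum, and the SAP can be followed exactly without adjusting for it. Bias arises only if both open defecation and APO risk differ by setting after the five listed covariates are taken into account. Its size and direction cannot be derived from the SAP. Under the assumed splits, with no true effect, the spurious risk ratio runs from 1.00 to 1.40 crude, and from 1.00 to 1.18 if the listed covariates absorb half of the setting difference. The study is powered for a ratio of 1.5, so bias of this order could matter, but the SAP does not show that it will occur.

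**What to change.** Name block (four levels), or at least district, as a prespecified covariate or stratum in every adjusted model for APO, preterm birth and low birth weight. Make the covariate paragraph refer to that same list. Report the exposure effect within each setting as supportive only: with settings of equal size, each would hold about 285 of the 570 evaluable women.

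State the expected open defecation prevalence by setting, and the power that follows: about 72% at a 70/30 split and 60% at 80/20, against 79% with no imbalance. Block adjustment may cost somewhat more than district adjustment if exposure also varies between blocks within a district.

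Otherwise the change is SAP wording. Each woman's block should already be known, since the sample is drawn from a census of named blocks, so no new data collection is expected.

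### The SAP plans to collect maternal height but does not commit to adjusting for it; BMI is a poor stand-in, so a modest, conditional bias in the sanitation risk ratio is left open (minor)

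*SAP*

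**What the plan says.** In the SAP, Study Exposure Measures, part B (covariates and confounders), the interview and personal measurements are to include "anthropometric characteristics such as height and weight". Height is therefore planned as a baseline covariate.

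The section headed Statistical Analysis Plan then names the variables regarded in advance as confounders: maternal age; "BMI, maternal haemoglobin as indicator of maternal nutritional status"; and household poverty and maternal education for socio-economic status. Height is not named as a term of its own. The list is worded as a set of inclusions and is not declared complete.

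The covariate-adjustment paragraph, under Multiple comparisons and multiplicity, adds that the primary APO analysis will be adjusted for further baseline characteristics thought in advance to be associated with the outcome. It does not list them. No reason is given for carrying height and weight forward only as their ratio.

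**The concern.** BMI is weight divided by height squared, which removes most of the height information. A model with BMI but without height leaves stature nearly unadjusted.

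Adult height is fixed before pregnancy. First-trimester sanitation practice cannot change it, so adjusting for it cannot remove part of a real sanitation effect. If stature reflects early deprivation and is related to birth size (general subject knowledge, not something the SAP reports), it fits the plan's own idea of a confounder.

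The bias would be systematic and would run toward the study hypothesis, and a larger sample would not reduce it. Low birth weight, analysed separately as well as within APO, would be the most exposed outcome. The open adjustment clause also leaves the decision on height to be made after the data are seen.

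**Working it through.** **Inputs from the SAP (Sample Size and Power of the Study).** Two-sided alpha 0.05 ("Z-alpha= 1.96 at the for alpha of 0.05"), power 80%, APO risk 20% in the unexposed and 30% in the exposed, "ratio of exposed to unexposed which is approximately 1:1 in our study", 582 women before dropout.

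**The plan's own figure.**
- Unpooled variance: (1.96 + 0.84)² × (0.2×0.8 + 0.3×0.7) / 0.10² = 7.84 × 0.37 / 0.01 = 290.1, so 291 per group and 582 in total.
- Pooled variance without continuity correction, with unrounded normal quantiles: 294 per group, 588 in total.
- Power with 291 per group is 79.7%.

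The 582 reproduces, and adding height to the model leaves it as it is.

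**Does BMI carry height?** Assumptions: mean height 1.51 m, SD 5.5 cm, SD of log BMI at a given height 0.15, and weight proportional to height to the power p. Then log BMI varies with (p − 2) × log height, and the SD of log height is about 0.055 / 1.51 = 0.036. Simulated correlations of BMI with height:

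| p | correlation | share of height variance |
|---|---|---|
| 2 | 0.00 | 0% |
| 1.5 | -0.12 | 1.5% |
| 1 | -0.23 | 5.5% |

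BMI therefore carries at most about 6% of the variance in height over this range.

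**What could be left in the risk ratio?** Let d be the height difference between exposure groups, in SD, that remains after the named covariates. Let g be the odds ratio for APO per SD of shorter height. Neither is in the documents. With a logistic risk model and 20% risk in the unexposed, averaged over height:

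| d | g | apparent RR, true 1.0 | apparent RR, true 1.5 |
|---|---|---|---|
| 0 | any | 1.00 | 1.50 |
| 0.1 | 1.2-1.3 | 1.015-1.02 | 1.52-1.53 |
| 0.2 | 1.2-1.3 | 1.03-1.04 | 1.54-1.56 |
| 0.3 | 1.5 | 1.10 | 1.64 |

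Hand check at a true risk ratio of 1.0: apparent RR ≈ exp[(1 − 0.2) × d × ln g]. For d = 0.2 and g = 1.3 this is exp(0.8 × 0.0525) = 1.04. For d = 0.3 and g = 1.5 it is exp(0.8 × 0.1216) = 1.10.

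**Scale.**
- At the design effect, SE of log RR = √(0.7/87.3 + 0.8/58.2) = 0.148, so the 95% interval around 1.5 is about 1.12 to 2.00.
- With no true effect and 20% risk in both groups of 291, SE = √(2 × 0.8/58.2) = 0.166. A spurious RR of 1.04 shifts the test statistic by ln(1.04)/0.166 = 0.24 and raises the two-sided error rate from 5% to about 5.6%. A spurious RR of 1.10 shifts it by 0.57 and gives about 9%.

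**The case against.** Four objections deserve weight.

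**Height is not excluded.** A reader might infer that height can enter the model only through BMI. The text does not support that: the named list is not closed, and the covariate-adjustment paragraph would admit height. This objection stands. What remains is that the plan permits height without committing to it.

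**A larger bias is tempting.** Suppose exposed women are 0.35-0.5 SD shorter and each SD of height multiplies risk by 0.80-0.85. Then 0.85^(−0.35) = 1.06 and 0.80^(−0.5) = 1.12. Those figures cannot be read as the bias of the planned model unless that whole gap survives adjustment for poverty and education, which partly block the same pathway. If half survives (an assumption), the range is 0.85^(−0.175) = 1.03 to 0.80^(−0.25) = 1.06. If none survives, it is 1.00. On the other side, the poverty measure is itself described as a proxy. The study also draws on a coastal rural and a mainland tribal setting, and site is not a named covariate. Some residual height difference is therefore possible, though not shown.

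**The premises come from outside the document.** The SAP reports no link between height and sanitation practice or between height and APO. The concern can only be put conditionally. The composite also counts preterm birth, abortion and stillbirth, so an effect acting through birth weight would be diluted in APO, though not in low birth weight analysed alone.

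**This is covariate preference.** Partly so: the plan makes no false statement here. But height is planned for collection under the covariates heading, it is fixed before exposure, and the proxy actually named carries almost none of its information. Nothing in the objections shows that including height would do harm.

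**Conclusion.** The point holds as a minor one. Height is planned for collection, is not a named model term, and is poorly represented by BMI. Whether it enters the analysis is left undecided.

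Any bias depends on a height difference between exposure groups remaining after the named adjustments. If open defecators remain the shorter group and shortness raises APO risk, the bias is away from the null: none at a residual difference of 0, 1.015-1.04 at 0.1-0.2 SD with odds ratios of 1.2-1.3 per SD, and about 1.10 at 0.3 SD with an odds ratio of 1.5. All of these inputs are assumptions. At the modest values the bias lies well inside the study's interval of 1.12 to 2.00 around its design effect, so it would be unlikely to overturn a finding of that size.

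A reader should not conclude that stature confounding is established in this study, nor that height will be available for every woman. The SAP states a plan to collect it, not its completeness.

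**What to change.** In the SAP section headed Statistical Analysis Plan, add maternal height (continuous, in cm) to the covariates named in advance, as a separate term alongside BMI, in the APO, preterm birth and low birth weight models.

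The cost is one line of text and one degree of freedom per model. No new data are needed and the sample size stands. No further women should be lost to missing covariates, because a BMI calculated from measured height and weight already requires height.
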